### Compliance analysis

2.4

Descriptive statistics on compliance will be performed. Compliance will be evaluated by the average of the daily compliance during the 4 weeks of the study. As the product will be consumed in the first feeding bottle of the day, parents will have to report if the bottle feeding is totally consumed and/or if there is any regurgitation.

Daily compliance will be calculated as follows:

((Volume of milk with study product drunk − Volume of milk regurgitated)/Volume of milk to be drunk) × 100

### Safety analysis

2.5

All AEs will be listed, and descriptive statistics (imputability and intensity) of all the registered AEs will be provided by product. Infant growth endpoints (e.g., weight, height, and head circumference) will be analyzed using the same ANCOVA model used to analyze the primary endpoint. The proportion of subjects showing at least 1 AE will be compared between groups using a chi-Square or Fisher's exact test. The number of events will be compared between groups using a Poisson regression.

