### Design and setting

3.1

This is a randomized, double-blind, placebo-controlled, 2-parallel-group trial, which will be conducted in the Shanghai First Maternity and Infant Hospital, Shanghai, China. Participating infants will undergo a 2-week run-in period and then be randomly allocated (at a 1:1 ratio) to receive either an oral probiotic product or an identical placebo once daily for 4 weeks, with a follow-up period of 8 weeks. Therefore, the duration of the subjects’ participation will be 14 weeks, with a total of 5 visits. Each parent who agrees to have his or her infant enrolled in the trial will sign an informed consent form; the study protocol has been approved by the Medical Ethics Committee of Shanghai First Maternity and Infant Hospital. The current study will be performed in accordance with the standards of the International Committee on Harmonization of Good Clinical Practice and the revised version of the Declaration of Helsinki.

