### Participant and eligibility

3.2

Two hundred infants, aged 4 to 6 months, will be included in this study. As no detailed data were available in the literature about the primary endpoint of the present study in the target population of interest, no formal sample size calculation has been performed. To meet the recommendations of the Chinese Center for Disease Control and Prevention (CCDC) (≥ 50 subjects per group) and anticipating a high drop-out rate, it has been decided to include 100 infants in each group of the study. The Committee on Nutrition of the European Society for Paediatric Gastroenterology, Hepatology, and Nutrition (ESPGHAN) has concluded that the administration of probiotic-supplemented infant formula during early life (≤ 4 months of age) does not result in any consistent clinical effects.^[20]^ The World Health Organization (WHO) recommends that infants start receiving complementary foods at the age of 6 months. Thus, the age of 4 to 6 months will be applied for the inclusion of subjects.

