**Figure 2 F2:**
[figure not shown]
Clinic schedule of the trial.

During the first visit (V1), a face-to-face interview will be conducted with the participant's parents. An investigator (pediatrician) will explain the study procedures in detail, particularly the purpose of the study, the procedures to be undergone, and the potential risks and benefits of participation. The inclusion and exclusion criteria will be reviewed to determine if the participant qualifies for the study. If the parents agree to have their infant enrolled in the trial, one of them will sign an informed consent. At the same time, the investigator will collect relevant information on demography, medical history, and concomitant medications.

During this first visit, parents can choose any brand of milk powder in the list of allowed infant formulas (without probiotics; if with prebiotics, GOS < 2 g/100 g and no FOS inside) presented by the investigators. The investigators will recommend the Biostime Infant Formula (Biostime Inc., Guangzhou, China). If parents are willing to choose the Biostime Infant Formula from the list, they will be provided a free and sufficient supply of the Biostime Infant Formula. The infant's feeding will have to be completely switched to the new infant formula within 1 week (D1-D8).

A saliva sample will be obtained at the site by the investigators at V1 (D1), V2 (D15), and V3 (D44). Parents will be instructed to collect a stool sample of their infant at home at V1 (before starting the new infant formula), V2 (within 24 h before the visit time), and V3.

The infant's diaries will be provided to parents at each visit, and they will be instructed to fill in these diaries daily from D8 to D99 in order to record GI symptoms (Bekkali scale),^[22]^ crying episodes (number and duration), number of stools, compliance (volume of milk of the first feeding bottle actually drunk, planned to be drunk, and regurgitated), and potential concomitant medications. Moreover, a physical examination will be conducted at each visit, and potential adverse events (AEs) will be monitored throughout the trial by the investigators.

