### Safety assessment

3.10

An adverse event (AE) has been defined as any unfavorable or unintended clinical or other occurrence during the study period that may or may not be causally related to the intervention. All AEs considered not, unlikely, possibly, probably, or definitely related to the test product will be recorded in the CRFs.

A serious AE is defined as event that is fatal, life-threatening, disabling, or incapacitating or results in hospitalization, a prolonged hospital stay, or malformation. All will be also recorded in the CRFs, whether they are related to the test product or not. Probiotics are generally considered safe and well tolerated, and any serious AEs that might be possibly, probably, or definitely related to the test product will be regarded as unexpected. All serious AEs will be reported as soon as possible to the national Food and Drug Administration (FDA) and local FDA, the sponsor, and Infant Hospital. Any serious AEs that might be related to the test product will immediately lead to the discontinuation of the test product, and the study subject will be followed until the conclusion of the event.

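### Poisson comparison of AE counts is specified without a term for clustering within infants or for follow-up time, so its error rate depends on assumptions that the data may not meet

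*Protocol article*

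**What the plan says.** Section 2.5 (Safety analysis) plans three things for AEs.

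- Description: "descriptive statistics (imputability and intensity) of all the registered AEs will be provided by product".
- A comparison of infants: "The proportion of subjects showing at least 1 AE will be compared between groups using a chi-Square or Fisher's exact test".
- A comparison of events: "The number of events will be compared between groups using a Poisson regression". No offset, dispersion parameter, robust variance or counting window is given, and none is ruled out.

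Four other places bear on this.

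- Section 3.10 (Safety assessment) defines an AE as "any unfavorable or unintended clinical or other occurrence during the study period that may or may not be causally related to the intervention". Section 3.7 adds that "potential adverse events (AEs) will be monitored throughout the trial by the investigators".
- Sections 3.1 and 3.7 give a 2-week run-in, then 1:1 randomisation, 4 weeks of product and 8 weeks of follow-up, 14 weeks in all.
- Section 3.2 chose 100 infants per group while "anticipating a high drop-out rate". No dropout rate is stated.
- Section 3.12 lists the numbers of AEs and serious AEs among the secondary endpoints.

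**The concern.** Poisson regression takes the variance of each infant's count to equal its mean. AEs in infants tend to cluster: some have several minor illnesses or digestive complaints and others have none. The variance then exceeds the mean, the model's standard error is too small, and chance differences between the products reach significance too often.

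The outcome is also a number of events, not a rate. An infant who leaves early has less time in which to have an AE. If one group loses more infants, that group looks safer for that reason alone.

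Finally, the AE definition covers the run-in, when no product has been given. Counting those events under a product would pull a real difference towards no difference. At stake are the p-value and interval for a safety comparison in healthy infants.

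**Working it through.** The article gives no AE rate, dispersion or dropout figure, so there is no stated result to reproduce. The inputs from the document are 100 infants per group, 2 + 4 + 8 = 14 weeks, randomisation at week 2, and a 0.05 significance level (taken as two-sided). All other inputs are assumptions, shown as ranges.

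**1. Clustering.** Let φ be the variance/mean ratio of the counts. The true standard error of the log count ratio is √φ times the Poisson one, so

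true type I error = 2 × [1 − Φ(1.96/√φ)].

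Under a negative binomial with mean μ AEs per infant and dispersion k, φ = 1 + kμ.

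| φ (assumed) | example | √φ | 1.96/√φ | type I error |
|---|---|---|---|---|
| 1 | k = 0 | 1.00 | 1.96 | 0.050 |
| 1.5 | μ = 1, k = 0.5 | 1.22 | 1.60 | 0.110 |
| 2 | μ = 1, k = 1 | 1.41 | 1.39 | 0.166 |
| 3 | μ = 2, k = 1 | 1.73 | 1.13 | 0.258 |

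**2. Dropout.** Suppose a fraction d leaves at times spread evenly over the 12 weeks after randomisation. Mean observed time, run-in included, is 2 + 12(1 − d) + 6d = 14 − 6d weeks. With equal true rates, the expected count ratio is the ratio of these times:

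- 40% v 20%: 11.6/12.8 = 0.91.
- 50% v 30%: 11.0/12.2 = 0.90.
- Equal dropout at any level: 1.00.

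Simulation (100 per group, 10,000 replicates per setting) agrees, with mean ratios of about 0.90 to 0.91 under unequal dropout and 1.00 under equal dropout. Without clustering, the type I error of the unadjusted Poisson test is 0.057 to 0.070 under equal dropout of 30% or 50%, and 0.10 to 0.17 under unequal dropout. The omission of follow-up time therefore does little harm unless the groups differ in it.

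**3. Run-in.** If the AE rate is the same in all weeks except for a true ratio R after randomisation, counting all 14 weeks gives (12R + 2)/14:

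- R = 1.5: 20/14 = 1.43.
- R = 2.0: 26/14 = 1.86.

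In simulation with μ = 1, no clustering and no dropout, power to detect 1.5 is 0.84 without the run-in and 0.78 with it.

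**4. Does the remedy work?** In the same simulations with a true ratio of 1, across μ = 1 and 2, k = 0, 0.5 and 1, and all dropout patterns tried:

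- Offset alone brings the ratio back to about 1.00. Type I error stays at about 0.10 to 0.25 when k is 0.5 or 1.
- Offset with robust variance gives type I error of 0.050 to 0.057 and a mean ratio of 0.99 to 1.00.

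Both parts are needed.

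**The case against.** The strongest objection is that this is silence, not error. The article condenses a fuller protocol, its SAP is not shown, and Poisson regression is routinely fitted with a log-time offset and a scaled or robust variance. A reader might infer that the plan fixes a model without follow-up time and counts run-in events in it. The documents do not say so. The AE definition and the monitoring statement govern what is recorded, and the sentence on all registered AEs concerns description, not the regression. That part of the objection stands.

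It does not remove the point. The article is specific about its other models: Sections 2.2 and 2.3 write out the terms, the SAS procedure and, for repeated diary measures, a random subject effect. For events that can recur within an infant, Section 2.5 commits to a named model whose standard variance assumption is doubtful for such data, and a better one is available.

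Three further objections also stand and limit the size of the point.

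- Small standard errors come from clustering. Missing follow-up time and run-in counting are not their main source.
- Section 3.2 expects high dropout overall and says nothing of a difference between groups. Without a difference there is no bias in the ratio.
- Run-in events precede randomisation, so they are balanced in expectation. They dilute a difference and cannot create one systematically.

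**Conclusion.** The point holds in a conditional form, at low to moderate severity. If AE counts are overdispersed and the variance is left uncorrected, the Poisson test is too liberal: about 11%, 17% and 26% at assumed variance/mean ratios of 1.5, 2 and 3. If dropout differs by some 20 percentage points (assumed) and no exposure term is used, the ratio is off by about 10%, in favour of the group that loses more infants. Counting run-in events would dilute a ratio of 1.5 to 1.43.

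It would go too far to say that the safety p-value and interval are wrong. The article gives no AE data from which to judge the dispersion, and no dropout figures by group. Nor does the safety conclusion rest on this one test. The comparison of infants with at least one AE does not use the Poisson variance, although it too ignores follow-up time, and all AEs are listed.

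**What to change.** Reword the sentence in Section 2.5, and carry it into the SAP, along these lines:

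- Compare AE counts by negative binomial regression, or by Poisson regression with robust variance, with log of each infant's post-randomisation follow-up time as offset. Report the rate ratio with its 95% confidence interval.
- Count only AEs that start after the first sachet, and list run-in AEs separately. Sachets are handed over at V2, so randomisation and first sachet should lie close together, but the count and the offset should use the same starting point.
- Report follow-up time and withdrawals by group beside the AE results.

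The change needs no extra visits or infants. It does need AE onset dates and the date of last contact. The article does not mention onset dates explicitly, so the sponsor should confirm that the CRF holds them. The cost is wider intervals where counts are overdispersed: by the factor √φ on the log scale, or 1.22 to 1.73 at the ratios assumed above. An offset treats the AE rate as constant over follow-up and withdrawal as unrelated to AE risk, so marked differences in withdrawal would still need discussion.

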## Results

3

### Design and setting

3.1

This is a randomized, double-blind, placebo-controlled, 2-parallel-group trial, which will be conducted in the Shanghai First Maternity and Infant Hospital, Shanghai, China. Participating infants will undergo a 2-week run-in period and then be randomly allocated (at a 1:1 ratio) to receive either an oral probiotic product or an identical placebo once daily for 4 weeks, with a follow-up period of 8 weeks. Therefore, the duration of the subjects’ participation will be 14 weeks, with a total of 5 visits. Each parent who agrees to have his or her infant enrolled in the trial will sign an informed consent form; the study protocol has been approved by the Medical Ethics Committee of Shanghai First Maternity and Infant Hospital. The current study will be performed in accordance with the standards of the International Committee on Harmonization of Good Clinical Practice and the revised version of the Declaration of Helsinki.

### Participant and eligibility

3.2

Two hundred infants, aged 4 to 6 months, will be included in this study. As no detailed data were available in the literature about the primary endpoint of the present study in the target population of interest, no formal sample size calculation has been performed. To meet the recommendations of the Chinese Center for Disease Control and Prevention (CCDC) (≥ 50 subjects per group) and anticipating a high drop-out rate, it has been decided to include 100 infants in each group of the study. The Committee on Nutrition of the European Society for Paediatric Gastroenterology, Hepatology, and Nutrition (ESPGHAN) has concluded that the administration of probiotic-supplemented infant formula during early life (≤ 4 months of age) does not result in any consistent clinical effects.^[20]^ The World Health Organization (WHO) recommends that infants start receiving complementary foods at the age of 6 months. Thus, the age of 4 to 6 months will be applied for the inclusion of subjects.

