### Inclusion criteria

3.3

Each infant will have to meet all of the following criteria to be enrolled in this study:♦Good health♦Single birth♦Gestational age ≥ 37 weeks (WHO)♦Birth weight ≥ 2500 g♦Appropriate weight at inclusion visit between P20 and P80 in accordance with the weight percentile charts of Chinese children aged 0 to 18 years^[21]^♦Aged > 4 months (120 days) and < 6 months (180 days)♦Being exclusively formula-fed (no breast milk meal) at the inclusion visit♦No gastrointestinal diseases within 1 month (CCDC)♦No use of antibiotics within 1 month (CCDC)♦Parents’ agreement to use one of the recommended infant formulas [no probiotics; if with prebiotics, galacto-oligosaccharides (GOS) < 2 g/100 g and no fructo-oligosaccharides (FOS) inside]♦Consent form signed by at least one of the parents or a legal guardian♦Parents able to understand the protocol requirements and to fill in the infant's diaries

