### Study procedure and clinic schedule

3.7

Participants will be required to pursue a 2-week run-in, 4-week intervention, and 8-week follow-up period. The duration of subjects’ participation will be 14 weeks, with total 5 visits: inclusion (Visit 1, Day 1), start of intervention (V2, D15), end of intervention (V3, D44), and follow-up (V4 and V5, D72 and D100) (Figs. 1 and 2).

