## Discussion

4

In the early stage of life, the composition of the intestinal microbiota undergoes major modifications, mostly influenced by feeding patterns.^[23]^ Intestinal microflora composition differs substantially in breast-fed infants and formula-fed infants because of the differences in composition between human milk and standard infant formula. The breast-fed infant's microbiota is composed of an increased number of *Bifidobacteria* and *Lactobacilli*, whereas the formula-fed infant's microbiota has more *Enterococci* and *Enterobacteria.*^[24,25]^ It is widely accepted that breast-fed infants are often healthier than formula-fed infants and can fight infections better. This difference is considered to be due to breast milk's composition with molecules with antimicrobial activity and prebiotic oligosaccharides with various health benefits.^[26,27]^ In fact, healthy intestinal microflora are essential to infants’ health, and the composition of intestinal microflora could be adapted by consuming probiotics in infancy.^[28]^ Therefore, the first 2 to 3 years of life are the most critical period in which one can intervene to shape the microbiota as best as possible, and so optimize child growth and development.

Numerous randomized controlled trials have shown that the use of probiotic products, including those that are added to commercially available infant formula and other food products for children, is effective in preventing and treating common diseases such as diarrhea and allergy.^[29,30]^ However, little is known about whether probiotics could offer benefits to healthy infants. With the boom of probiotics appearing on the market, the use of probiotic products in the community is becoming more widespread.^[31]^ It is therefore important to provide sufficient scientific evidence for its effectiveness in the digestibility and immunity of exclusively formula-fed healthy infants. An effective, practical, and acceptable intervention for these infants would represent a major clinical and public health advance. If cost effective, the simplicity of the intervention is such that the administration of probiotic supplementation or follow-on formula to infants, given beyond early infancy, may be associated with some clinic benefits. However, it is worth noting that despite there currently being no safety concerns regarding probiotics, more research is required regarding the long-term and routine use of probiotic-supplemented formula to healthy infants.

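### The upper age limit is justified by complementary foods starting at 6 months but applied only at V1, so it does not cover the V2–V3 period of the primary endpoint

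*Protocol article*

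**What the plan says.** Participant and eligibility (3.2) gives two reasons for the age window. The one for the upper end is "The World Health Organization (WHO) recommends that infants start receiving complementary foods at the age of 6 months", and the section concludes: "Thus, the age of 4 to 6 months will be applied for the inclusion of subjects".

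Inclusion criteria (3.3) puts the window in days, "Aged > 4 months (120 days) and < 6 months (180 days", and dates the feeding criterion to the same moment: "Being exclusively formula-fed (no breast milk meal) at the inclusion visit". Study procedure and clinic schedule (3.7) places the eligibility check at V1: "The inclusion and exclusion criteria will be reviewed to determine if the participant qualifies for the study". The same section sets the visits: "inclusion (Visit 1, Day 1), start of intervention (V2, D15), end of intervention (V3, D44), and follow-up (V4 and V5, D72 and D100".

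Study endpoint (3.12) defines the primary endpoint as the V3 minus V2 change in seven faecal bacterial groups. Primary analysis (2.2) models it on product, V2 value and their interaction. Secondary analysis (2.3) uses the same model for salivary SIgA and adds paired V2 versus V3 tests within each group. Randomization and blinding (3.5) balances on delivery method and breastfeeding history. Age appears in neither the allocation nor the model.

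**The concern.** The only reason given for stopping at 6 months is that infants are then expected to start other foods. A limit set for that reason would serve its purpose if infants were still below it when the outcome is measured. Here it is tested 14 days before the baseline stool sample and 43 days before the final one, so many infants can satisfy it at V1 and be past it at V3.

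Two things are at stake. First, infants at different stages of feeding and gut maturation may change by different amounts between V2 and V3 whatever the product. That adds variance to the primary endpoint, in a trial which by its own account had no formal sample size calculation and so has no demonstrated margin of power. Second, the paired within-group tests have no control for ageing or diet at all.

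**Working it through.** **Inputs.** Admissible V1 age is above 120 and below 180 days (3.3). V1 is D1, V2 is D15 and V3 is D44 (3.7). The age distribution within the window is not given, so it is assumed below and varied.

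**Offsets.** Age at a visit = age at V1 + (visit day − 1).
- V2: +14 days. An infant is past 180 days at V2 if older than 180 − 14 = 166 days at V1.
- V3: +43 days. An infant is past 180 days at V3 if older than 180 − 43 = 137 days at V1.
- The primary endpoint spans 44 − 15 = 29 days.

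**Even spread over 120 to 180 days.**
- Past 180 days at V2: (180 − 166)/60 = 14/60 = 23%.
- Past 180 days at V3: (180 − 137)/60 = 43/60 = 72%.
- Crossing between V2 and V3: (43 − 14)/60 = 29/60 = 48%.

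Counting completed days (121 to 179, 59 values, at or past 180) gives 14/59 = 24%, 43/59 = 73% and 29/59 = 49%. Only 16 of those 59 ages (27%) remain under 180 days at V3. Taking 6 months as 183 days gives 19% at V2 and 68% at V3.

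**Other age distributions.** Write t = (cut-off − 120)/60, so t = 46/60 for V2 and 17/60 for V3.

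| Assumed V1 ages | Mean (days) | Share past 180 days | At V2 | At V3 | Crossing V2–V3 |
|---|---|---|---|---|---|
| Even | 150 | 1 − t | 23% | 72% | 48% |
| Linear, towards young | 140 | (1 − t)² | 5% | 51% | 46% |
| Steeper, towards young | 135 | (1 − t)³ | 1% | 37% | 36% |
| Linear, towards old | 160 | 1 − t² | 41% | 92% | 51% |
| Peaked mid-window | 150 | 1 − t²(3 − 2t) | 14% | 80% | 67% |

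A majority are past 180 days at V3 unless intake is strongly skewed to the youngest, with a mean V1 age below about 140 days. Whether a majority cross inside V2–V3 depends on the assumed shape; under an even spread it is just under half.

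**What added variance would cost.** The article gives no standard deviation, so this is illustrative only. If age- and diet-related change raised the variance of the V2–V3 change by a fraction v, 100 infants per arm would carry the information of 100/(1 + v): 90.9 for v = 0.10 and 80 for v = 0.25. The actual v is unknown.

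**The case against.** - **The rationale is worded for inclusion.** Section 3.2 applies the window to the inclusion of subjects and nowhere promises a diet free of other foods through V3. That is a fair reading, and it means the text does not flatly contradict itself. What stands is that a reason about other foods has little bearing on the primary endpoint if it no longer holds when that endpoint is measured.
- **Reaching 180 days is not the same as starting solids.** This stands. A reader might infer that most infants begin solids during treatment. The article does not say when they begin, and under even intake about 48% cross 180 days inside V2–V3. The Discussion's remark that feeding patterns shape the microbiota is followed by a contrast between breast and formula feeding; it does not mention solids.
- **Randomisation protects the main comparison.** This also stands. Allocation is 1:1 and blinded, age precedes treatment, and the model adjusts for each infant's V2 value. A reader might infer that diet change biases the product effect, but the design does not support that. Chance imbalance in age is already covered by the type I error rate. The protection does not extend to the within-group tests.
- **The population is described correctly in the criteria.** Section 3.3 dates exclusive formula feeding to the inclusion visit and explains it as no breast milk. A reader might infer that the infants measured at V3 are no longer the stated population; this is not shown. Only the Abstract and the Discussion, with "effectiveness in the digestibility and immunity of exclusively formula-fed healthy infants", omit the timing.
- **The diary may record other foods.** The listed diary items do not include them, but the full protocol, diary and case report form are not shown. Their absence from the article is not counted as a fault.

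**Conclusion.** The point holds as a mismatch between the stated reason for the upper age limit and the visit schedule. Under even intake about 23% of infants are past 180 days at V2 and 72% at V3, with about 37% to 92% at V3 across the skewed distributions tried. The offsets follow directly from the schedule; the percentages rest on the assumed age distribution.

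The consequence is limited. The between-arm comparison remains valid. The cost is possible extra variance in the primary endpoint, of unknown size, and direct confounding of the within-group V2 versus V3 tests with 29 days of ageing and any change in diet. That diet or age moves these particular outcomes is an inference, not something the article quantifies.

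**What to change.** 1. **Add age at V2 as a prespecified covariate** in the primary ANCOVA (2.2) and in the same model for SIgA (2.3). Age is already known and precedes treatment, so this costs one degree of freedom per model. It recovers only the part of the variance related to age.
2. **State that the within-group V2 versus V3 tests are descriptive** and will not be read as evidence of a product effect. No cost.
3. **Record the date of first non-formula food** with one line in the existing diary, if it is not already there. Tabulate it by arm, and do not adjust for it, because it arises after randomisation. Small cost.
4. **Describe the population as exclusively formula-fed at inclusion** in the Abstract and Discussion, in line with 3.3. No cost.
5. **Reconcile the age rationale in 3.2 with the visit schedule in 3.7**, for example by saying that the limit concerns feeding at enrolment and that many infants will be past 6 months by V3.

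Two larger changes are not recommended. Applying the 180-day limit at V3 would cut the 60-day recruitment window to about 17 days (137 − 120). A supportive analysis in infants under 137 days at V1 would hold about 17/60 × 100 ≈ 28 per arm under even intake, before the high drop-out that 3.2 anticipates and below the minimum of 50 per group cited there.
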